**Trial registration number:**

ISRCTN15374803.

STRENGTHS AND LIMITATIONS OF THIS STUDYAll eligible patients waitlisted for heart transplant (in one of the only two centres in the UK that perform paediatric heart transplant) will be approached and prospectively recruited and followed up in this study to minimise selection bias.As a phase I trial with primary focus on establishing safety of the cellular therapy at a range of doses, the study participants will not be randomised (or blinded) and results will not be able to quantify biological efficacy of Treg on cardiac allograft vasculopathy in a small population of patients with statistical significance.However, the immuno-monitoring schedule and analysis of data from patient biospecimens (collected before and after delivery of the therapy) will seek to study how the immune system of patients changes with cellular therapy administration to provide further information about the biological effect of the Tregs (which can be studied further in future studies).

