## Methods and analysis

### Study design

This is a phase I, open label, single-centre clinical trial investigating two different dose banding ranges (1–3×10^6^ cells/kg and 5–10×10^6^ cells/kg) of autologous thymus derived Tregs (TR006) in nine paediatric heart transplant recipients. All clinical and patient-facing activity (including dosing) will occur at GOSH in London, UK.

When a suitable organ is available for a recruited study patient (see figure 2), their thymus tissue will be collected during surgery. This tissue will be transported to the GMP Facility at Guy’s Hospital National Health Service (NHS) Foundation Trust and will form the starting material for the IMP production under GMP conditions, as outlined in the manufacturing section below.

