**Figure 2 F2:**
[figure not shown]
Schematic to highlight the key events in generating the investigational medicinal product (IMP) TR006 for ATT-Heart. IMP, Investigational Medicinal Product.

Each child will progress through the routine post-operative care pathway (see figure 2). Standard of care immunosuppression will be maintained in all ATT-Heart trial patients and there are no plans to reduce it in this study.

Thymus tissue will be procured prior to the first dose of Basiliximab (anti-CD25 antibody that will affect Treg function) or other induction agent that might be given in theatre. Planned study procedures for ATT-Heart follow routine surveillance including endomyocardial biopsies at 14 days, 3 months and 6 months post-transplant in all patients. At 3 months, in addition to cardiac biopsy, coronary imaging (intravascular ultrasound (IVUS) or coronary angiogram) will be performed in children who weigh more than 25 kg. The outcome from the 3-month biopsy, particularly a negative result for histopathological signs of rejection, will be confirmed prior to administering TR006 to the patient.

Each study patient will receive a single dose of TR006 at 3–6 months post-transplant after initial baseline safety investigations are completed as per the study’s eligibility criteria. They will be monitored in hospital during and after the infusion for one night followed by further safety investigations prior to discharge the next day. Regular study visits as part of the safety monitoring stage will include investigations such as echocardiograms, 12 lead electrocardiograms and blood tests (clinical and research), before and after TR006 dosing. Please refer to onlinesupplemental tables 2  3 for details.

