### Intervention description: dose escalation strategy

Participants will receive a 10 mL single dose of TR006 at 1–3×10^6^ TR006/kg or at 5–10×10^6^ TR006/kg.

A single ascending dose design will be followed with groups of three patients in three cohorts. The first cohort of three patients will receive a lower dose of 1–3×10^6^ Tregs cells/kg and if no Dose-limiting Toxicities (DLTs) occur, then the second cohort (of three patients) will be given a higher dose of 5–10×10^6^ Treg cells/kg. The third cohort of three patients will receive the highest tolerated dose of Tregs from the second cohort (up to a maximum of 10×10^6^ Treg cells/kg).

These dose ranges were selected to match what we estimate to be the minimal anticipated biological effect doses based on the ThRIL and ONE study.^17 20^ Of note, the dose escalation schedule in ATT-Heart is more conservative than previous Treg trials conducted in children in Poland,^14^ the USA^16^ and Spain.^21^ However, as this is the first clinical trial in the UK with thymus derived Tregs, our priority is to determine safety of the IMP, as agreed with the Medicines Healthcare products Regulatory Agency (MHRA).

We will monitor biological activity of Tregs in vivo in this study. However, we plan to conduct further dose escalation and formally investigate biological efficacy in a future phase II trial if this trial confirms initial safety in patients and feasibility of manufacturing initial dose ranges.

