### Immuno-monitoring specific integrative data analysis plan

We will continue to prioritise Treg enrichment because our primary mechanistic questions are whether Tregs can be tracked by T Cell Receptor (TCR) clonality over time and how their phenotype and state changes post-infusion. To that end we will run 10× Chromium X 5’ captures on FACS-enriched Tregs with paired TCR VDJ. This preserves depth on a rare population and gives a robust clonotype map.

To provide the broader immune context, we will also perform whole-PBMC single cell (sc) RNA-sequencing with Cellular Indexing of Transcriptomes and Epitopes (CITE)-sequencing. We will employ cell hashing to multiplex samples and control cost. CITE-sequencing and TCR-sequencing will be generated from the same 10× capture so this approach will not compromise gene-expression depth on the enriched Treg runs. Further details on the time points are below.

We will use endomyocardial biopsies at day 14, month 3 and month 6 (ie, 3 months post-Treg infusion) and profile them by 10× Xenium. From each biopsy, we will focus on analysis of regions around small vessels to quantify endothelial activation, perivascular myeloid and lymphoid niches, fibroblast and matrix programmes and the presence of FOXP3+T cells. We will place control and Treg arm biopsies on the same slide to control for batch effects.

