The primary clinical outcome is coronary allograft vasculopathy progression measured by IVUS (or coronary angiography in younger children) as the change in mean intimal thickness from month 3 to month 12, together with the prespecified CAV grade at month 12. Although CAV is defined in the coronary arteries, it is driven by immune and stromal processes that are reflected in the myocardial microvasculature. The spatial assay reads out those processes in situ. We will derive quantitative spatial features from the day 14, month 3 and month 6 biopsies, including endothelial activation scores, perivascular immune neighbourhood metrics and fibroblast remodelling signatures, and link them prospectively to the subsequent IVUS change between month 3 and month 12. We will aim to produce models that adjust for clinical covariates and integrate the circulating single cell RNA sequencing signals from the matched blood samples. This provides a biologically coherent bridge from tissue level mechanisms in myocardium to arterial remodelling in the coronaries. We will therefore test whether changes in spatial endothelial and perivascular signatures are linked to CAV progression, and whether these are modified in patients receiving TR006.

In short, the myocardial biopsies supply early spatial readouts of vascular inflammation and remodelling, the matched blood provides systemic context and Treg tracking, and both are linked prospectively to IVUS-based CAV progression between month 3 and month 12.

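### The only stated batch rule for the biopsy assay needs a control arm that the trial does not have, and it does not protect the within-child change that is analysed

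*Protocol article*

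**What the plan says.** All references are to the protocol article.

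- **Assay and time points** (Immuno-monitoring specific integrative data analysis plan): "We will use endomyocardial biopsies at day 14, month 3 and month 6 (ie, 3 months post-Treg infusion").
- **Batch rule** (same section): "We will place control and Treg arm biopsies on the same slide to control for batch effects". No other batch measure is given for the biopsies.
- **Analysis** (same section): the investigators will "test whether changes in spatial endothelial and perivascular signatures are linked to CAV progression", and will also ask whether these are altered in children given TR006.
- **Blood single-cell work** (same section): "We will employ cell hashing to multiplex samples and control cost". The samples to be pooled are not named.
- **Design** (Study design): "This is a phase I, open label, single-centre clinical trial investigating two different dose banding ranges", in nine children.
- **Cohorts** (Intervention description: dose escalation strategy): "A single ascending dose design will be followed with groups of three patients in three cohorts".
- **Who is treated** (Study design, text after Figure 2): "Each study patient will receive a single dose of TR006 at 3–6 months post-transplant".
- **Allocation** (strengths and limitations list): "the study participants will not be randomised (or blinded"). The same list describes the biospecimen analysis as a comparison of samples taken before and after the therapy.

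**The concern.** The article chose to state how batch effects will be controlled, and the measure it states serves a treated-versus-control contrast. Nothing else in the article supplies a control group: every child is treated, and no external or historical source of biopsies is described. The second spatial question, whether the signatures differ in children given TR006, depends on the same missing group.

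The main contrast that nine treated children can give is change within child. The month-3 result is confirmed before dosing, so day 14 and month 3 are pre-infusion and month 6 is the post-infusion biopsy. A comparison of dose bands is also possible, but it sets 3 children against at most 6. The stated rule does nothing for the change score unless matched untreated tissue is on every slide at every time point.

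At stake is whether a shift in endothelial or perivascular signatures after infusion can be read as biology rather than as a difference between slides. The layout has to be settled before the assay is run.

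**Working it through.** The article gives no power, variance or error-rate figure for the spatial assay, so there is nothing to reproduce. The calculation below is an illustration under stated assumptions.

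**Inputs**
- Children: 3 cohorts × 3 = 9 (dose escalation section).
- Biopsies: 9 × 3 = 27 at most (day 14, month 3, month 6).
- Two-sided 5% level, the level the Data analysis plan gives if any comparison is made.
- Assumed: per-biopsy SD = 1, and an additive slide effect with SD r in the same units. The document does not give r; the range is 0.25 to 1.5.
- Assumed for the power figures: a true change of 1.5 SD.

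**Variance of a child's change between two biopsies**
- Same slide: the slide effect cancels, so the variance is 2 × 1 = 2 (SD 1.41).
- Separate slide for each biopsy: 2 × (1 + r²).
- Ratio: 1 + r².

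**Mean change in nine children.** Power uses the noncentral t with 8 df.

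**One slide per time point.** Every child's change then contains the same shift, with variance 2r². The mean change has variance 2/9 + 2r², but its standard error is estimated from the between-child spread, which does not contain the shift. The t statistic is therefore inflated by √[(2/9 + 2r²)/(2/9)] = √(1 + 9r²): 1.25, 1.80 and 3.16 for r = 0.25, 0.5 and 1.0. Type I error was simulated with 200,000 runs.

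| r | Variance ratio, separate slides | Power, same slide | Power, separate slides | Type I error, one slide per time point |
|---|---|---|---|---|
| 0 | 1.00 | 79.5% | 79.5% | 5.0% |
| 0.25 | 1.06 | 79.5% | 77.1% | 10.2% |
| 0.5 | 1.25 | 79.5% | 70.4% | 23.7% |
| 1.0 | 2.00 | 79.5% | 50.7% | 48.7% |
| 1.5 | 3.25 | 79.5% | 34.3% | 63.0% |

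**Association of change with IVUS progression.** A shift common to all children goes into the intercept and does not bias the slope, so the last column does not apply to this analysis. Independent slide effects do weaken it. The SD of change grows by √(1 + r²), so a correlation is multiplied by 1/√(1 + r²): 0.97, 0.89 and 0.71 for r = 0.25, 0.5 and 1.0.

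**The case against.** The strongest reply is that the layout argument rests on silence. The same-slide rule is compatible with a slide that holds all three of a child's biopsies, and slide layout is the kind of detail an article leaves to the full protocol or a laboratory manual. This stands as far as it goes. A reader might infer that the plan scatters a child's biopsies over slides or runs them by time point; the article says neither. What the reply does not remove is that the one measure the article does state refers to an arm absent from its own design.

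A reader might also infer that batch and biology could never be separated afterwards. That is too strong, for two reasons. The association with IVUS change is unbiased by a common shift, and reference tissue on every slide would allow correction. Control biopsies could serve as that reference if they existed, which is why leaving them undefined matters.

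A third tempting reading is that cell hashing leaves the blood data open to capture effects. The article gives multiplexing as well as cost as its purpose, and pooling hashed samples in one capture can reduce capture effects. Nothing says that a child's visits are split.

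Blocking by child also has a price. The plan relates features of individual biopsies, not only changes, to later IVUS change between children. With one child per slide, child and slide are aliased for those features and for dose-band comparisons. This stands and shapes the fix.

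Finally, the work is exploratory in a nine-child safety trial, and the article says that statistical comparisons are unlikely. That limits the weight of the point.

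**Conclusion.** The point holds in a limited form. As written, the batch rule cannot be carried out in the described trial, and it does not protect the within-child change that the integrative analysis uses. This follows from the text alone.

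The size depends on a layout and an r that the article does not give. For r from 0.25 to 1.0, separate slides raise the variance of change by 6% to 100%. A layout with one slide per time point and no shared reference would raise the type I error of a mean-change test to between 10% and 49%. These figures assume additive slide effects, nine complete children and a test of mean change, which the article does not specify. They show what a poor layout would cost and are not evidence that one is planned.

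Neither the primary endpoint nor the dose-escalation decisions are touched. It is still worth correcting before any section is run, because a layout confounded with time and lacking a reference cannot be repaired from those data.

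One related inconsistency bears on the same change score. The section equates month 6 with three months after infusion, whereas dosing may take place at 3–6 months after transplant, so the month-6 biopsy could fall about 0 to 3 months after infusion. Those passages must be reconciled.

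**What to change.** 1. Define the source of the control biopsies (who they come from, how many, at which time points), or delete the reference to a control arm and the treated-versus-untreated question that depends on it.
2. Run each child's day-14, month-3 and month-6 biopsies on the same Xenium slide. Where space allows, put several complete children on each slide. Randomise position, and add a section from one common reference tissue to every slide.
3. Include slide as a factor in the models. For comparisons of levels between children, rely on shared slides or on the reference section.
4. As a suggestion only, for blood: pool a child's pre-infusion and early post-infusion samples in one hashed capture where feasible, or carry a bridging sample across captures. Pooling every visit is not advised, because research samples continue to 24 months after dosing.

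**Cost.** This is a layout decision for at most 27 biopsies. Spatial read-out waits for the month-6 biopsy, or for that of the last child where several share a slide. Earlier tissue is stored longer than later tissue, and the reference sections take up slide area. If only one child fits on a slide, between-child level comparisons depend wholly on the reference section.

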Parents or carers of children who are listed for heart transplant at GOSH will be approached by the research team with written information about the study. Where possible, children will also be given information about the trial with age-appropriate patient information sheets to explain the study process. This may happen during their routine clinical appointment or at the time of transplant assessment with plans to obtain informed consent from potential participants (and their parents/carers) ahead of transplant surgery occurring. In certain cases, children on the heart transplant waiting list may require interim open-heart surgery by midline sternotomy for placement of a left ventricular assist device or commencing central mechanical support as a bridge to transplant; in which case thymus tissue may be procured at this stage.

Children who have had historical midline sternotomy procedures will be excluded from this trial as thymus tissue may have been previously resected.^51^ Furthermore, children with conditions such as DiGeorge syndrome may have T cell deficiency or be born with absent thymus will also be excluded from this trial.^52^

All efforts will be made to approach patients and carers who are eligible for this study prior to heart transplant surgery. In cases where transplant surgery has to happen in a short time frame for clinical reasons, interim consent to collect thymus tissue to commence manufacture of cell therapy will be sought from the parents/guardians during surgical consent before obtaining full consent at a later date to remain in the trial (to include TR006 administration and safety follow-up). This staged consent approach was incorporated into the study design on recommendation by the Research Ethics Committee in order to optimise the opportunity for patients requiring urgent transplantation surgery to enter this trial.

Typically CAV is a long-term complication of heart transplant; however, if there are signs of early CAV on the 3 month coronary imaging in a patient, we still plan to enrol them into the study and continue follow-up and coronary imaging at month 12 post-transplant as per the protocol. The presence and establishment of CAV post-transplant carries with it a poor prognosis as described in the study rationale.^1 5^

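### The month-6 biopsy lies inside the month 3 to month 12 IVUS interval, so the change is not subsequent to it and its link to that change is not prospective

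*Protocol article*

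**What the plan says.** The section on the immuno-monitoring integrative data analysis plan defines the imaging outcome as "the change in mean intimal thickness from month 3 to month 12", together with a CAV grade at month 12. On the predictor side it states: "We will derive quantitative spatial features from the day 14, month 3 and month 6 biopsies". It will then "link them prospectively to the subsequent IVUS change between month 3 and month 12". The closing sentence of the section says the same of the biopsies and the matched blood: "both are linked prospectively to IVUS-based CAV progression between month 3 and month 12".

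The clock is fixed elsewhere in the article. Study design (text after Figure 2) places "endomyocardial biopsies at 14 days, 3 months and 6 months post-transplant in all patients" and sets the baseline imaging: "At 3 months, in addition to cardiac biopsy, coronary imaging (intravascular ultrasound (IVUS) or coronary angiogram) will be performed", for children above 25 kg. The recruitment section refers to "continue follow-up and coronary imaging at month 12 post-transplant as per the protocol". Study design also requires the month-3 biopsy result to be confirmed before TR006 is given, and allows infusion at 3–6 months after transplant.

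**The concern.** A measurement can be called prospective for a change only if it is taken before that change begins. The sentence applies one temporal order to all three biopsies, and one of them falls while the outcome is accruing. Endothelial activation or perivascular infiltrate seen at month 6 may precede later thickening, accompany it, or follow thickening that took place between months 3 and 6. A link with the whole month 3 to 12 change does not separate these explanations.

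The month-6 biopsy is also the one on which any treatment-related reading depends. Day-14 and month-3 tissue is obtained before infusion. The section intends to test whether changes in spatial signatures are linked to CAV progression and whether TR006 modifies them, and only month 6 can carry that information. At stake is what the trial may say about temporal order in that analysis.

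**Working it through.** The plan gives no figure for this analysis, so there is nothing to reproduce. The check is date arithmetic, followed by an illustration.

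**1. Time order (months after transplant).** Inputs: biopsy times from Study design and the integrative plan; imaging times from Study design (month 3) and the recruitment section (month 12).

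- Outcome interval: 12 − 3 = 9 months.
- Day-14 biopsy: before the interval, so the change is subsequent to it.
- Month-3 biopsy: at the start of the interval, so the wording is acceptable.
- Month-6 biopsy: 6 − 3 = 3 months into the interval; 3/9 = 33% has elapsed. The change is not subsequent to it.

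Matched month-6 blood is in the same position, as is any change score with month 6 as an end point. A day-14 to month-3 change would be correctly ordered, but it is wholly pre-infusion.

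**2. Can the outcome be restarted at month 6?** That would need coronary imaging at month 6. The article names months 3 and 12 only, so a month 6 to 12 change cannot be formed from the imaging it describes.

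**3. Position relative to infusion.** The plan describes the biopsy as "month 6 (ie, 3 months post-Treg infusion". With infusion allowed at 3–6 months, the gap runs from 6 − 6 = 0 to 6 − 3 = 3 months, so the description fits only a child infused at month 3. Month 6 is still the only listed biopsy that can follow infusion.

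**4. Illustration of the consequence (assumed values, not trial figures).** Suppose the month 3–6 and month 6–12 changes are independent, with variance proportional to time. Suppose a month-6 feature correlates r with the month 3–6 change and has no relation to later change. Then

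correlation with the month 3–12 change = r × √(3/9) = 0.577 × r.

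| Assumed r | Correlation with month 3–12 change | Correlation with month 6–12 change |
|---|---|---|
| 0.3 | 0.17 | 0 |
| 0.5 | 0.29 | 0 |
| 0.7 | 0.40 | 0 |
| 0.9 | 0.52 | 0 |
| 1.0 | 0.58 | 0 |

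A simulation with 400,000 draws agreed with the formula to within 0.003. Under these assumptions, a feature that carries no information about later change still shows an association of up to 0.58 with the outcome as defined.

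**The case against.** The strongest reply is that the section speaks of linking, which is already the language of association, and that *prospectively* may only mean planned, forward data collection. The first part stands: a reader might infer that the trial will report month-6 features as predictors of CAV, but the text does not say so. The second part does not rescue the sentence, because *subsequent* states a time order and that order is wrong for month 6.

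Other stronger readings are not supported either:

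- A reader might infer that a spatial marker will be carried into phase II as predictive. The article says only that clinical and immune-monitoring data will support identification of a dose.
- A reader might take this to be the central mechanistic question. The plan names Treg tracking by TCR clonality, and change in Treg phenotype and state after infusion, as its primary mechanistic questions.
- A reader might conclude that there is no month-6 imaging. That is inferred from the article text; the visit tables are in a supplement that is not shown. Even if such imaging exists, the stated outcome still starts at month 3.
- A reader might assume a defined month-3 to month-6 change score. The plan does not say between which biopsies changes will be taken.

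It is also fair to say that the outcome includes a CAV grade at month 12, assessed six months after the month-6 biopsy. This weakens the point without removing it: without imaging at month 6, the grade may reflect disease already present then.

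Finally, modelling detail for exploratory work commonly sits in an analysis plan that is not shown. The point here, however, is a temporal order that the article itself states incorrectly.

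**Conclusion.** The point holds, limited to the month-6 biopsy, its matched blood and any change score using month 6. The IVUS change from month 3 to month 12 is not subsequent to a measurement taken 3 months into those 9 months, and an association found there could reflect thickening that has already occurred. The time-order finding rests only on dates in the article. That a month 6 to 12 change cannot be formed rests on the imaging the article names. The correlations of 0.17 to 0.58 rest on assumed independence, variance proportional to time and no relation to later change; they show that the problem can arise, not how large it will be in this trial.

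The scale is modest. This is an exploratory mechanistic analysis in at most nine children, with month-3 coronary imaging limited to those above 25 kg. The dose-limiting toxicity endpoint is untouched. The wording should still be corrected, because it governs what may be concluded about temporal order from the only listed biopsy that can follow infusion.

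**What to change.** In the integrative data analysis plan, keep *prospectively* and *subsequent* for day-14 and month-3 features only. Analyse month-6 features, matched month-6 blood and any change score that uses month 6 separately, labelled as concurrent association with CAV change and with no claim of temporal order. Correct the closing sentence of the section in the same way. Where month-6 features are set against the month-12 CAV grade, state that disease already present at the month-6 biopsy cannot be excluded on the imaging described.

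The cost is wording and a split of the analysis: no added samples, visits or imaging, and no data lost. The downside is a more modest claim for the month-6 data. The change is best made before results are known.
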